### Control arm

Patients randomized to the control arm will be managed according to normal hospital rehabilitation practice. Three months postoperatively patients will receive instructions for home exercises in a single individual guidance session. The exercise program will consist of light muscle endurance (abdominal crunch, bird dog exercise, forward lunge, posterior pelvic tilt), mobility (hamstring stretch, lateral flexion of thoracic spine), and balance exercises (one-leg standing). Patients will be instructed to perform the home exercises 3 times per week.

### Outcomes

The outcome measurements will be assessed at baseline (3 months postoperatively), at the end of the exercise intervention period (15 months postoperatively), and after a 1-year follow-up. Only primary outcome variables will be used in the 27 months follow-up assessment.

#### Primary outcome variables

The intensity of back and lower limb pain during rest and daily activities in the past week will be assessed by means of the visual analogue scale (VAS) [41]. Disability due to back pain during the past week will be assessed by the Finnish version of the Oswestry Low Back Pain Disability Questionnaire 2.0 [42]. Quality of life will be evaluated by the Finnish version of the generic SF-36 Health Survey Questionnaire [43].

#### Secondary outcome variables

##### Physical function/fitness

Maximal isometric forces of the trunk flexors and extensors will be measured using a strain-gauge dynamometer [44]. Endurance strength of the trunk extensors will be measured by the Biering-Sorensen test [45,46]. Spinal mobility towards flexion will be measured by the Schober and Stibor tests [47] and fingertip–floor distance tests [45], and lateral bending by the method described by Frost et al. [48]. The intensity of pain during the trunk muscle strength and mobility measurements will be assessed with a VAS. The ‘timed up and go’ test (TUG) will be used to assess functional mobility (power, walk velocity, agility and dynamic balance) [49].

##### Kinesiophobia

The TSK will be used to measure the subjective experience of fear of movement [50].

##### Assessment of physical activity and exercise adherence

The amount of physical activity will be evaluated by the short form of the International Physical Activity Questionnaire (IPAQ) [51]. Training diaries will capture the frequency of the back-specific exercises and pedometers will be used to assess the total amount of daily steps in the intervention arm. The number of aerobic steps (10 minutes of continuous walking more than 60 steps per minute) during one week will be reported at least every second month.

## Statistical analysis

### Sample size

Cristensen et al. [7] estimated that a sample of ~60 patients (30 per group) is necessary to achieve 85% power for detecting a 25% difference in disability over time (baseline to 1 year), or at a follow-up of a 1 year, with a one-sided significance α-level of 0.05. However, we assume the between-group difference in pain will be lower in our participants. Assuming a dropout rate of 15-20% at the 1-year follow-up, we aim to include at least 80 patients (preferably 100) in our sample.

The clinical outcome variables will be analyzed by the intention-to-treat principle with the last observation carried forward (LOCF). The normality of variables will be evaluated by the Shapiro-Wilk statistic. Statistical comparison between the arms will be done using the chi-square test, Fisher's exact test, bootstrap-type analysis of covariance (ANCOVA) or multivariate analysis of variance (MANOVA) with Pillai’s trace statistics. A multiple imputation (Markov-chain Monte Carlo) method will be applied to supply possible missing values of individual questionnaire items, when appropriate.

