**Methods/design:**

In the present RCT-study we aim to assess the effectiveness of a combined back-specific and aerobic exercise intervention for patients after LSF surgery. One hundred patients will be randomly allocated to a 12-month exercise intervention arm or a usual care arm. The exercise intervention will start three months after surgery and consist of six individual guidance sessions with a physiotherapist and a home-based exercise program. The primary outcome measures are low back pain, lower extremity pain, disability and quality of life. Secondary outcomes are back function and kinesiophobia. Exercise adherence will also be evaluated. The outcome measurements will be assessed at baseline (3 months postoperatively), at the end of the exercise intervention period (15 months postoperatively), and after a 1-year follow-up.

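### The minimum of 80 is little more than another trial's 60 plus dropout, so it leaves almost no room for the smaller difference the plan expects, and the borrowed power is one-sided

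*Protocol article*

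**What the plan says.** The Sample size section of the protocol article gives one power statement, attributed to an earlier rehabilitation trial: "a sample of ~60 patients (30 per group) is necessary to achieve 85% power". The effect is described as "detecting a 25% difference in disability over time (baseline to 1 year), or at a follow-up of a 1 year", and the test as "with a one-sided significance α-level of 0.05".

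The section then departs from that effect: "However, we assume the between-group difference in pain will be lower in our participants". It gives no size or SD for the lower difference. The next sentence sets the number: "Assuming a dropout rate of 15-20% at the 1-year follow-up, we aim to include at least 80 patients (preferably 100) in our sample".

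The Methods/design part of the Abstract states a single figure: "One hundred patients will be randomly allocated to a 12-month exercise intervention arm or a usual care arm". The Abstract and the section on primary outcome variables list back pain, leg pain, disability and quality of life as primary.

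The analysis paragraph plans intention-to-treat with last observation carried forward (LOCF). For comparing arms it names the chi-square test, Fisher's exact test, bootstrap-type ANCOVA, and MANOVA with Pillai's trace.

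**The concern.** A smaller expected difference calls for more patients before dropout is added. The paragraph announces the smaller difference, but its minimum is about what dropout inflation of the borrowed 60 would give with no change in effect.

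Two further features weaken the link between the borrowed figure and this trial:

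- **Outcome.** The borrowed effect concerns disability and the adjustment concerns pain. It is unclear which of the primary outcomes drives the number.
- **Sidedness.** The borrowed level is one-sided. MANOVA with Pillai's trace and the chi-square test have no direction, and ANCOVA and Fisher's test are ordinarily two-sided. The article declares no one-sided analysis.

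If recruitment ended near 80, a null result could be read as evidence against an effect that the trial had limited power to detect.

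**Working it through.** **Inputs from the Sample size section:** 30 per group, 85% power, 25% difference, one-sided 0.05; dropout 15-20%; minimum 80, preferred 100.

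**Assumptions (mine):** two-sample t-test, equal arms, and an SD that stays constant as the difference shrinks. The article gives no SD, so the borrowed 60 cannot be derived independently; it can only be solved backwards.

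**Step 1. Dropout inflation, N/(1 - dropout).** 60/0.85 = 70.6, so 71. 60/0.80 = 75. The minimum of 80 exceeds these by 9 and 5.

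**Step 2. Completers.** 80 × 0.85 = 68 (34 per arm); 80 × 0.80 = 64 (32 per arm). 100 × 0.85 = 85 (42.5 per arm); 100 × 0.80 = 80 (40 per arm).

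**Step 3. Implied standardised effect.** Normal approximation: d = (z0.95 + z0.85) × √(2/30) = (1.645 + 1.036) × 0.258 = 0.692. The noncentral t gives d = 0.7005, so 25% corresponds to about 0.70 SD. Two-sided power for that d with 30 per arm is 76%.

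**Step 4. Detectable difference at 85% power,** converted as 25% × d/0.7005:

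| Enrolled | Completers per arm | One-sided 5% | Two-sided 5% |
|---|---|---|---|
| 80 | 32 to 34 | 24.2% to 23.5% | 27.2% to 26.3% (d 0.761 to 0.738) |
| 100 | 40 to 42.5 | about 21.7% to 21.0% | 24.2% to 23.5% (d 0.678 to 0.658) |

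**Step 5. Power with 80 enrolled, completers only.** The 22.5% and 20% rows are illustrations, because the plan gives no value:

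| True difference | One-sided 5% | Two-sided 5% |
|---|---|---|
| 25% | 87-89% | 79-81% |
| 22.5% | 80-82% | 70-73% |
| 20% | 72-74% | 60-62% |

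With 100 enrolled, power for 20% is 80-82% one-sided and 70-72% two-sided.

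**Step 6. Enrolment for 85% one-sided power at 20%.** This needs 94 completers: 94/0.85 = 110.6, so 111; 94/0.80 = 117.5, so 118.

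**Step 7. Most favourable unadjusted case.** If LOCF keeps all 80 in the analysis (40 per arm) with no dilution of the effect, two-sided power for 25% is 87% and the difference detectable at 85% power is 24.2%. For an effect of 20%, two-sided power is 70%.

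**The case against.** Four objections carry weight.

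- **Nothing is miscalculated.** 80 does cover dropout inflation of 60, and one-sided it reaches slightly below 25%. This stands. The weakness lies in the justification, not in the arithmetic.
- **The shortfall has no stated target.** The plan never sizes its lower difference, so 22.5% and 20% are illustrations. This stands too. On the completer basis, however, anything below about 23.5-24% has less than 85% power at 80 enrolled, even one-sided.
- **The planned analysis may do better than an unadjusted completer t-test.** LOCF gives the 87% ceiling in Step 7, although carrying baseline values forward may dilute the effect. Baseline adjustment with an assumed correlation of 0.5 multiplies d by √(1 - 0.25) = 0.866. The two-sided detectable values at 80 enrolled become 0.761 × 0.866 = 0.659 and 0.738 × 0.866 = 0.639, or 23.5% to 22.8%. That is below 25%, but still only a small allowance. The article gives no correlation and uses neither argument to justify its number.
- **A condensed article may leave the SD, alpha and power to a fuller document.** Their absence is therefore not the point. The point is that the reasoning printed here does not lead to the minimum printed here.

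A reader might also infer two stronger claims that the document does not support. The first is that 80 and 100 contradict each other. The Sample size section gives a floor and a preferred number, and the Abstract reports the preferred one; the target is loosely fixed, no more. The second is that the trial claims 85% power for its smaller difference. The 85% is attributed to the other trial, and the article states no power of its own.

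**Conclusion.** The concern holds as a moderate point about justification. The paragraph expects a smaller difference than its reference, yet the minimum it sets provides for almost none. Under one-sided testing, the difference detectable at 85% power moves only from 25% to 24.2-23.5%. Under two-sided testing, 85% power is not reached among completers even for the full 25%; it is reached only under the favourable LOCF assumption or with useful baseline adjustment.

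The percentages rest on reading 25% as 0.70 SD in a two-sample t-test with constant SD. The borrowed effect is described both as a change over time and as a follow-up difference, so the model behind it is not known. The comparison of 80 with 71-75 needs none of these assumptions.

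The 100 announced in the Abstract eases the problem but does not remove it. With 100 enrolled, the two-sided difference detectable at 85% power among completers is 24.2% to 23.5%, the same as 80 gives one-sided.

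**What to change.** 1. Make the Abstract's 100 the single target in the Sample size section.
2. Replace the borrowed power statement with this trial's own. At two-sided 5% with 80-85 completers, the detectable difference is 0.63-0.61 SD at 80% power, or 0.68-0.66 SD at 85%, before baseline adjustment. If a gain from adjustment is claimed, state the assumed correlation; with 0.5, the first figure becomes 0.634 × 0.866 = 0.55 SD.
3. Tie the statement to one named primary outcome, chosen by the sponsor, with its SD, so that disability and pain are no longer mixed.
4. Do not present 80 as sufficient for a difference smaller than the reference trial's.

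The cost is one rewritten paragraph and no patients beyond the 100 already announced. The downside is that the stated figure becomes less favourable than the borrowed one.

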### Study arms

The intervention arms will start three months postoperatively and will last 12 months.

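### LOCF is fixed for the clinical outcomes although nothing is measured between months 3 and 15, so patients lost before month 15 are scored as unchanged and the estimated effect can be biased

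*Protocol article*

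**What the plan says.** The second paragraph under Sample size in the Statistical analysis section sets the rule: "The clinical outcome variables will be analyzed by the intention-to-treat principle with the last observation carried forward (LOCF"). The same paragraph adds: "A multiple imputation (Markov-chain Monte Carlo) method will be applied to supply possible missing values of individual questionnaire items, when appropriate". It names no other method, and no sensitivity analysis, for a visit that is missed altogether.

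Under Outcomes, measurements are "assessed at baseline (3 months postoperatively), at the end of the exercise intervention period (15 months postoperatively"), and once more a year later. For that last visit, "Only primary outcome variables will be used in the 27 months follow-up assessment". The Study arms section places the whole programme between the first two assessments: "The intervention arms will start three months postoperatively and will last 12 months".

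On expected losses the plan says: "Assuming a dropout rate of 15-20% at the 1-year follow-up, we aim to include at least 80 patients (preferably 100) in our sample". It does not split this rate by arm.

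**The concern.** LOCF needs a recent observation to carry. Here the only value before month 15 is the baseline itself, so at month 15 LOCF is baseline carried forward. A patient who leaves during the programme is analysed as if pain, disability and quality of life had stayed exactly where they were three months after surgery. Secondary outcomes have a single post-baseline visit, so for them LOCF can never be anything else.

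The month-15 comparison of the arms is at stake. It is diluted when dropout is equal. When dropout is unequal and patients go on changing after month 3, it is shifted in a direction that cannot be known in advance. Unequal dropout is plausible: one arm has six guidance sessions and a 12-month home programme, the other a single session, and patients know their allocation. The 27-month comparison, which is there to test persistence, is affected as well.

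**Working it through.** **The plan's own figures.** The 30 per group taken from the cited study (85% power, one-sided α 0.05) cannot be rebuilt from its inputs, because no SD is given. Solved backwards, it implies a standardised difference of (1.645 + 1.036)/√15 = 0.692. Allowing for dropout, 60/0.85 = 71 and 60/0.80 = 75, so a target of at least 80 covers the stated loss of patients. That figure is not contested. However, recruiting more patients does not undo a bias.

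**Patients affected.** If 15–20% are lost by month 15, that is 12–16 of 80 or 15–20 of 100 patients whose month-15 value would be their month-3 value.

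**Bias at month 15.** Score improvement as positive. Let d1 and d0 be dropout before month 15 in the intervention and control arms, C the control-arm change from month 3 to month 15, and T the true effect. Assume that dropout is unrelated to outcome. Patients who drop out contribute zero change, so

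- expected LOCF difference = (1 − d1)(C + T) − (1 − d0)C
- bias = −d1·T − (d1 − d0)·C

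With equal dropout d, the second term vanishes and the estimate is (1 − d)T: 0.85T at 15% and 0.80T at 20%.

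**Illustration.** The documents give no T, C, SD, correlation or dropout by arm. The following are assumptions: 50 per arm, baseline/follow-up correlation 0.5, T = 0.60 SD, and C (recovery common to both arms) of 0.5 or 1.0 SD.

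| Dropout, intervention v control | C (SD) | T (SD) | Expected LOCF estimate (SD) |
|---|---|---|---|
| 20% v 20% | any | 0.60 | 0.80 × 0.60 = 0.48 |
| 25% v 10% | 0.5 | 0.60 | 0.75 × 1.10 − 0.90 × 0.5 = 0.375 |
| 25% v 10% | 1.0 | 0.60 | 0.75 × 1.60 − 0.90 × 1.0 = 0.30 |
| 10% v 25% | 0.5 | 0.60 | 0.90 × 1.10 − 0.75 × 0.5 = 0.615 |
| 10% v 25% | 1.0 | 0.60 | 0.90 × 1.60 − 0.75 × 1.0 = 0.69 |
| 25% v 10% | 1.0 | 0 | 0.75 − 0.90 = −0.15 |
| 20% v 20% | any | 0 | 0 |

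Simulation of an ordinary ANCOVA under these inputs, tested two-sided at 0.05, agrees with the table and gives the error rates:

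- T = 0.60, 20% v 20%: power is about 83%, 78% and 69% for common recovery of 0, 0.5 and 1.0 SD, against about 86% on observed data.
- T = 0.60, 25% v 10%: power is about 55% and 34% for recovery of 0.5 and 1.0 SD.
- T = 0, 25% v 10%, recovery 1.0 SD: type I error is about 13%. The shift is −0.15 SD, so these are mostly false findings against the intervention.
- T = 0, equal dropout: type I error stays near 5%.

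**Month 27.** With equal dropout, let a be the fraction lost before month 15 and b the fraction lost between months 15 and 27. The first group carries baseline (no effect) and the second carries the month-15 effect T15, so

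- bias = b(T15 − T27) − a·T27

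Take T15 = 0.6, T27 = 0.3 and a = b = 10%. The bias is then 0.10 × 0.3 − 0.10 × 0.3 = 0. More late dropout makes it positive and more early dropout makes it negative.

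**The case against.** The strongest defence is that LOCF here is mild and conservative. With equal dropout it only shrinks the effect, type I error stays near 5%, and the larger distortions need unequal dropout together with substantial recovery after month 3. The documents give figures for neither, and the Background notes that disability after fusion may stay high. All of this stands as a limit on size. It does not rescue the method: shrinkage follows from equal dropout alone whenever the effect is real, and with more dropout in the control arm and continuing recovery LOCF can overstate the effect, so it is not reliably conservative.

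The dropout figure is also ambiguous. The plan's phrase for the 1-year follow-up may mean month 15 or month 27. If it means month 27, fewer patients are lost by month 15. At an assumed 10%, for example, 0.60 SD becomes 0.90 × 0.60 = 0.54 SD rather than 0.48 SD.

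Three stronger readings are tempting and are not supported:

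- A reader might infer that the 27-month result is biased towards a maintained effect. Carrying month-15 values does hide later change in patients lost after month 15, but those lost earlier carry baseline, so the net bias can go either way.
- A reader might infer that the standard errors are wrong because filled-in values count as observed. In the simulated scenarios the empirical SD of the estimate and the model standard error agree (for example 0.194 v 0.193). The defect shown is bias in the estimate.
- A reader might infer that the intervention arm will lose more patients. Six sessions could equally improve retention.

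Finally, the simulation makes dropout unrelated to outcome, which favours analysis of observed data. Outcome-related dropout was not examined. A separate analysis plan might add sensitivity analyses, but the rule stated here is LOCF.

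**Conclusion.** The point holds. The article fixes a rule that, on its own visit schedule, records zero change for everyone lost before month 15, and its multiple imputation does not reach missed visits. Under dropout that is equal and unrelated to outcome, 15–20% of any real effect is lost if the plan's dropout rate applies at month 15, and possibly less if it refers to month 27. This part rests on algebra and the plan's own rate.

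Under unequal dropout with continuing change, the bias can go in either direction. The 0.30 SD, 0.69 SD and 13% figures show how large it could be, but they depend on an effect size, a recovery, a correlation and a dropout split that the documents do not give. If there is no true effect and dropout is equal and unrelated to outcome, there is no bias in the mean. At month 27 the direction of the net bias cannot be stated.

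**What to change.** Replace LOCF as the primary handling of missed visits by one of the following:

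- **(a) A likelihood-based repeated-measures model** on all randomised patients. Either take the 15- and 27-month values as responses and the 3-month value as covariate, with arm, visit, arm × visit, diagnosis and centre; or take all three visits as responses with baseline means constrained equal across arms and no baseline covariate. The 3-month value must not enter both as response and as covariate. For outcomes measured only at month 15, use ANCOVA with visit-level multiple imputation.
- **(b) The MCMC multiple imputation already planned**, extended from questionnaire items to missed visits and done by arm.

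Keep LOCF at most as a sensitivity analysis. It would also help to say whether the 15–20% dropout refers to month 15 or month 27.

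The cost is about one sentence of text and slightly more analysis work, with no extra patients or data. Both options rely on a missing-at-random assumption, which the text should state.

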### Randomization and blinding

After surgery, the participants will be randomized into either the combined back-specific (combination of strength training and training of control of the neutral lumbar spine position) and aerobic training arm or to the control arm. The allocation will be based on computer randomization in blocks of four patients. The randomization will be performed and the randomization lists maintained by the research nurses, who will not be involved in the assessment or treatment of the participants. The first list will be used to randomize the participants with isthmic spondylolisthesis and the second list to randomize those with degenerative spondylolisthesis. Both centres will have their own randomization lists. Assessors will be blind to the treatment group in both study centres. Physiotherapists will not be blind to group membership; instead, but both study arms will have their own physiotherapist who will carry out postoperative guidance. Blinding the patients to the allocation is not possible due to the nature of the intervention.

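### Randomisation is stratified by diagnosis and centre, but the analysis text provides for neither factor and leaves ANCOVA or MANOVA open for the primary outcomes

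*Protocol article*

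**What the plan says.** **Allocation.** Under Randomization and blinding, the protocol article states: "The allocation will be based on computer randomization in blocks of four patients". On diagnosis: "The first list will be used to randomize the participants with isthmic spondylolisthesis and the second list to randomize those with degenerative spondylolisthesis". On site: "Both centres will have their own randomization lists". Two diagnoses in two centres give four lists, each with blocks of four.

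**Analysis.** The second paragraph under Sample size gives the methods in one sentence. It begins "Statistical comparison between the arms will be done using the chi-square test" and continues with Fisher's exact test and then bootstrap ANCOVA or MANOVA, the last with Pillai's trace. Just before it stands: "The normality of variables will be evaluated by the Shapiro-Wilk statistic". The paragraph names no covariate for the ANCOVA, mentions neither diagnosis nor centre, and assigns no outcome to a method.

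**Outcomes.** Primary outcome variables lists back and leg pain on a visual analogue scale, the Oswestry questionnaire and the SF-36. All are scores, so of the methods listed, ANCOVA and MANOVA are the ones that would apply to them.

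**The concern.** There are two separate matters.

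**Design and analysis do not visibly match.** Stratified blocks force the arms to be nearly equal on diagnosis and centre, so the true variance of the arm difference no longer contains variation between strata. A model without the strata still counts that variation as noise. Its standard error is then too large, and the benefit of stratifying is not collected.

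**The method for the primary outcomes is left as a choice.** ANCOVA estimates an adjusted between-arm difference in one outcome, in that outcome's own units. MANOVA with Pillai's trace asks whether the arms differ on any combination of several outcomes, and it gives neither a direction nor an effect size per outcome. One can reach significance when the other does not. With several primary outcomes and the two methods joined by an "or", a reader cannot tell which result would establish that the exercise programme works.

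**Working it through.** The article gives no figure for the effect of the strata, so there is none to reproduce. The numbers below answer one conditional question: what would be lost if the strata were left out?

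**Inputs from the article**
- Four strata and blocks of four (Randomization and blinding).
- A minimum target of 80 patients, with 15% to 20% dropout (Sample size).

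**Assumptions, not in the article**
- R², the share of outcome variance explained by the four strata: 0 to 0.20.
- Allocation 1:1 and a two-sided 5% test. The only stated level is one-sided 0.05, and it belongs to the earlier study's calculation.
- For the simulation: correlation of 0.5 between baseline and follow-up, and a true difference of 0.55 SD.

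**Formula.** When strata are balanced by design but omitted from the model:
- ratio of model standard error to true standard error = 1/√(1 − R²)
- real size = 2 × [1 − Φ(1.96/√(1 − R²))]

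For R² = 0.10, the ratio is 1/√0.90 = 1.054. The critical value becomes 1.96 × 1.054 = 2.066, and the size is 2 × [1 − Φ(2.066)] = 3.9%.

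**Simulation.** N = 80, four strata, permuted blocks of four, normal-theory ANCOVA on baseline with and without the strata, 6,000 replicates. The sampling error is about √(0.05 × 0.95/6000) = 0.3 points for size and √(0.8 × 0.2/6000) = 0.5 points for power.

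| R² | SE too large by (formula) | Size (formula) | Simulated size, without / with strata | Simulated power, without / with strata |
|---|---|---|---|---|
| 0 | 0% | 5.0% | 5.3% / 5.4% | 79.4% / 79.5% |
| 0.05 | 2.6% | 4.4% | 4.3% / 5.3% | 80.6% / 82.3% |
| 0.10 | 5.4% | 3.9% | 3.9% / 5.4% | 80.4% / 84.2% |
| 0.20 | 11.8% | 2.8% | 2.5% / 5.0% | 83.3% / 90.5% |

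The power lost is about 0, 2, 4 and 7 points. With 68 patients (80 × 0.85, after 15% dropout) it is about 0, 2, 5 and 10 points.

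**Scale of R².** In the formula, R² is the share of the variance that the model has to deal with. In the simulation it is the share of total outcome variance, and baseline already takes 0.5² = 0.25. The strata's share of what remains is therefore R²/0.75, which is 0.267 at R² = 0.20. The formula then gives 1/√(1 − 0.267) = 1.17, and the simulated standard errors agree (0.1948/0.1667 = 1.17). On the formula's own scale, without a baseline covariate and with the effect set for 80% power at R² = 0, the losses are smaller: 82.0 − 80.6 = 1.4, 84.0 − 81.3 = 2.7 and 87.9 − 82.7 = 5.2 points.

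**ANCOVA or MANOVA.** No arithmetic applies, because the article does not say which outcomes a MANOVA would cover or whether it would include baseline values.

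**The case against.** The strongest reply is that silence is not exclusion. An ANCOVA has covariates by definition, and a condensed article commonly leaves their list to the full protocol or the SAP, which are not shown. This largely stands. A reader might infer that the analysis ignores the stratification factors and so has wrong standard errors. The article does not say that. The harm needs two conditions, that the strata are omitted and that they are prognostic, and the article settles neither. Even then the error is conservative.

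MANOVA may also be meant as a global test across several primary outcomes, which is a reasonable use. But the text offers it as an alternative to ANCOVA and gives it no such role. That is more than a missing covariate list, because two non-equivalent methods are stated with nothing to choose between them.

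Three further inferences are tempting and should not be made:
- **That the Shapiro-Wilk result selects the test.** The article says only that normality will be checked. A bootstrap ANCOVA does not lean on normality, and MANOVA would be an odd fallback for skewed data.
- **That MANOVA would discard the baseline values, at a cost in sample size.** The article does not describe the MANOVA in that detail.
- **That power is already short.** The article gives no SD, so power cannot be computed. After 15% to 20% dropout, 80 patients leave 68 to 64, above the 60 of the earlier study. A smaller difference in pain is expected, but its size is not given.

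**Conclusion.** The point holds as an improvement at almost no cost. It is not an error that threatens validity. The article fixes a stratified design, its analysis text provides for neither factor, and it leaves the method for the primary outcomes open between two that answer different questions.

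The open choice rests on the printed text alone, and its effect cannot be sized from the article. The cost of omitting the strata is conditional. For an assumed R² of 5% to 20%, standard errors are about 3% to 12% too large (somewhat more if R² refers to total variance and baseline is in the model). The real size falls to about 4.4% to 2.8%, and about 2 to 7 points of power are lost at N = 80. With R² = 0 nothing is lost. At no point in the range does omission inflate false positives.

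**What to change.** State one primary comparison for each continuous primary outcome: bootstrap ANCOVA of the 15-month value on arm, with the baseline value, diagnosis (isthmic or degenerative) and centre as covariates, whatever the Shapiro-Wilk result. Report the adjusted difference with its confidence interval. Keep MANOVA with Pillai's trace as a supportive global test and name the outcomes that it covers. Reserve the chi-square and Fisher tests for categorical variables.

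The cost is a sentence or two in the analysis plan. Diagnosis and centre are known at randomisation, and the baseline scores are already scheduled. The strata use two degrees of freedom as main effects, or three as four separate strata. In the simulation with R² = 0 and N = 80, including them cost no power (79.4% without, 79.5% with). The target sample size does not change.
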